### Oversight and monitoring

#### Roles and composition of the trial management committee and trial steering committee

##### Principal investigators

Each participating region will have a lead investigator who will be the senior researcher receiving the public funding and will be responsible for identification and physician recruitment. Principal investigators will be steering committee members.

##### Research physicians

Any of the physician recruiting patients involved in the data collection and completion of CRFs, along with the follow-up of study patients and adherence to study protocol and investigators brochure.

##### Trial steering committee (TSC) (see title page for members)

All principal investigators will be steering committee members. Aragon region principal investigator will be national coordinator. Tasks: Agreement of final protocol. Recruitment of patients and liaising with principle investigator (PI). Reviewing progress of study and if necessary agreeing changes to the protocol and/or investigators brochure to facilitate the smooth running of the study.

##### Trial management committee (TMC)

There will be a principal investigator, a research physician, a statistician, and a administrator at each region. Tasks are as follows: study planning, organization of steering committee meetings, provide annual risk report and ethics committee serious unexpected suspected adverse events, responsible for trial master file, budget administration and contractual issues with individual centres, advice for lead investigators, audit of 6 monthly feedback forms and decide when site visit to occur, assistance with international review and board/independent ethics committee applications, data verification, and randomization (this in Madrid Region).

##### Data manager

There will be one per each region. Tasks are as follows: maintenance of trial IT system and data entry and data verification.

#### Composition of the data monitoring committee, its role, and reporting structure

A data monitoring committee (DMC) has been established based on the vital-status outcome measurement chosen and the long trial duration (18 months). The DMC is independent of the study organizers. For the data monitoring committee proposal, we have taken into account the distinguishing characteristics of pragmatic clinical trials [52–54]. This committee includes clinicians, biostatisticians, and ethical experts, and given the patient-centred outcomes focus of our trials [55, 56], a patient representative is incorporated to provide patient’s perspective. This will allow to review relative benefits, burdens, and potential harms of the interventions and will provide insight into the optimal ways for results sharing [57, 58] to participants and relevant patient group.

During the period of recruitment to the study, interim analyses will be supplied, in strict confidence, to the DMC, together with any other analyses that the committee may request. This may include analyses of data from other comparable trials. In the light of these interim analyses, the DMC will advise the TSC. The frequency of interim analyses will depend on the judgement of the Chair of the DMC, in consultation with the TSC. However, we anticipate that there might be one interim analysis at 12 months after randomization and one final analysis at 18 months. The interim analysis will be performed by an independent statistician, blinded for the treatment allocation. The statistician will report to the independent DMC.

### Statistical analysis

All analyses will be carried out according to the intention-to-treat principle, with a statistical significance at *p* < 0.05.

Description of the baseline characteristics means and standard deviations for the quantitative variables and absolute and relative frequencies for the qualitative variables, with their corresponding 95% confidence intervals (95% CIs). Likewise, the characteristics of those patients who leave the study will be described, including the reason for loss during follow-up.

Basal comparisons between groups will be performed using statistical tests for independent samples (Student’s *t*-test or chi-squared test). Tests for related samples (ANOVA for repeated measures) will be used to analyse changes within groups and between visits.

#### Analysis of main effectiveness

The difference in percentages in the composite endpoint of hospital admission or death to 18 months with its corresponding 95% CI. Multilevel analysis will be adjusted considering the combined final variable as the dependent variable; the baseline variables of the patient (first level), the professional (second level), and the intervention group as independent fixed effect variables; and the clustering by physician as a random factor. We will use multiple imputation by chain equations including baseline, 6-month, and 12-month data as available, intervention group, stratification and minimization variables, and other covariates that were informative of missingness. A sensitivity analysis will be conducted to assess whether conclusions may change if assumptions about missing data change.

#### Analysis of secondary effectiveness

The same analysis will be performed for 12 months. Missing data for professionals and/or patients will be replaced with the most recent reference or available data. For the remaining secondary effectiveness analyses, the difference in means or proportions will be calculated based on the characteristics of the variables (T3−T0) and (T2−T0) between groups using the appropriate statistical tests, and an explanatory model will be adjusted using the same methodology applied to the main outcome variable.

*Estimated quality-adjusted life years (QALYs)* gained at the population level, with corresponding 95% CI, as determined using parametric methods and bootstrap techniques. Given the 2-year time horizon, a discount rate of 3% will be applied.

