### Variables

FPs will provide their data before the start of the study. Patient data will be collected by the recruiting FP, who will also be responsible for patient follow-up. All information will be recorded in a case report form designed for the study. Each FP will access the form from their personal computer through the project website using a personal identification code. Four visits were defined for patient data collection: baseline (T0), 6 months (T1), 12 months (T2), and 18 months (T3) (see Table 1).

**Table 1 Tab1:** Visit plan

	T0 (baseline)		T1 (6 m*)	T2 (12 m*)	T3 (18 m*)	Responsible entity
Confirm inclusion/exclusion criteria	X					FP
Written informed consent	X					FP
Sociodemographic variables	X					FP
Morbidity variables and drug treatment plan	X		X	X	X	FP
Randomization of FP´s		X				RU
FP intervention (intervention group)		X				RT
Patient intervention (intervention group)			X	X	X	FP
Mortality				X	X	RT/FP
Hospitalizations				X	X	RT/FP
Functionality (WHODAS), falls, hip fractures			X	X	X	FP
Use of health services			X	X	X	RT
Quality of life	X			X	X	FP
Usability, adhesion, satisfaction			X		X	TG
Costs					X	RT

*T* time, *FP* family physician, *RU* research unit, *IG* intervention group, *RT* research team, *TG* technical group, *m** months from randomization

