#### Secondary outcome variables

All cause mortality, non-elective hospital admission (number of episodes and duration)Related to the use of medication: Potentially inappropriate prescription will be evaluated in accordance with the BEER criteria [39] and the STOPP-START criteria [40]; medication safety will be measured as the incidence of adverse reactions and potentially dangerous interactions, classified based on the taxonomy proposed by Otero-López [41] as well as the incidence of adverse reactions; and adherence to treatment will be measured. Medication adherence was measured with the Morisky Medication Adherence score [42].Use of health services will be measured using records of unplanned and/or preventable hospitalizations as well as the use of emergency services and PC (FP and nurse).Quality of life will be measured using the EQ-5D-5L questionnaire [43, 44]. The differences in utility index between the intervention group and the control group at 18 months of follow-up will be used to determine the QALYs gained due to the intervention. The scores or utilities derived from the latest version of this tool, the EQ-5D-5L, have been proposed to provide information on economic evaluations of technologies.Disability will be measured using the WHODAS questionnaire [45] and number of fractures.For cost-utility, the National Health Service perspective will be adopted, with a time horizon of 2 years and a discount rate of 3%. The costs incurred will be the time dedicated to training required by the training programmes, the cost of the teaching staff, the time dedicated to doctor-patient interviews, and the rights to use of the tool (DSS). All costs derived from the intervention will be charged through an opportunity cost proxy: average salary by professional category. As “avoided costs” of the intervention, we will consider the price of the drugs discontinued (measured using the retail price) and the cost of the adverse reactions avoided. The EQ-5D-5L questionnaire will be used to estimate the utilities in both groups (intervention and control). The QALYs obtained with the intervention will be calculated and compared with the difference between the costs incurred and avoided.DSS usability will be measured from user analysis perspective and usability testing [46] to the direct users (FPs): (a) User analysis: this analyses user behaviour while interacting with a website. It is going to be realized non-obtrusively in the background by recording mouse movements and click behaviour to identify to what extent functions and website areas are accessed when reviewing treatments (Hotjar Tool); (b) usability using an ad hoc design with the Spanish-validated System Usability Scale (SUS) [47] and Computer Software Usability Questionnaire [48], DSS acceptability will be measured using records of actions performed with the CheckTheMeds® algorithm (number of changes) and a review of time invested per professional, and DSS satisfaction will be measured using an ad hoc questionnaire.

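### The secondary analysis rule uses no observation time for admission and service-contact counts, needs a baseline value that Table 1 does not collect, and leaves the denominator for hospital duration undefined

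*Protocol article*

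**What the plan says.** The protocol article, Secondary outcome variables, lists "non-elective hospital admission (number of episodes and duration"), and measures health service use from "records of unplanned and/or preventable hospitalizations as well as the use of emergency services and PC". Falls and hip fractures appear in the abstract and in Table 1.

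Analysis of secondary effectiveness repeats the primary analysis at 12 months and then gives one general rule for everything else: "For the remaining secondary effectiveness analyses, the difference in means or proportions will be calculated based on the characteristics of the variables". The contrasts are T3−T0 and T2−T0 between groups, with appropriate tests. The section adds that "an explanatory model will be adjusted using the same methodology applied to the main outcome variable". That methodology, under Analysis of main effectiveness, is a multilevel model with patient and physician covariates and a physician random effect. No distribution, link or offset is named.

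On missing data the secondary section says: "Missing data for professionals and/or patients will be replaced with the most recent reference or available data". This differs from the multiple imputation planned for the primary outcome.

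The Variables section sets visits at "baseline (T0), 6 months (T1), 12 months (T2), and 18 months (T3"). In Table 1, hospitalizations are marked at T2 and T3 only. Use of health services is marked at T1, T2 and T3, as is the row "Functionality (WHODAS), falls, hip fractures". None of these rows is marked at T0.

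**The concern.** Admission episodes and emergency, physician and nurse contacts are counts that grow with time under observation. The stated contrast, model and replacement rule make no use of that time. If the latest available total of a patient lost at month 9 stands in for the 18-month value, nine months of contacts are treated as eighteen. The arm that loses more patients early then appears to use fewer services.

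Two further gaps concern the same outcomes. A change from T0 needs a T0 value, and Table 1 schedules none for them. Duration of admission could mean days per stay, days per admitted patient, or total days per randomised patient, and these can point in different directions if the intervention changes who is admitted. Admission is part of the primary composite, so the episode and duration results will be read as explaining the primary result.

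**Working it through.** **The plan's own figures.** The protocol gives no figure for these secondary outcomes. Its sample size shows which inputs can be relied on. Comparing 16% with 10% (the stated incidence less six points) at two-sided 5% and 80% power, pooled variance, gives 492 per group and 984 in total, as printed. Then 984 × 1.08 = 1062.7, printed as 1063, and 1063 × 1.08 = 1148, or 574 per group.

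**Inputs from the protocol:** 18 months of follow-up; 8% overall loss; 574 patients per group; intraclass correlation 0.02; eight patients per physician. The printed design effect of 1.08 uses five patients; eight gives 1 + 7 × 0.02 = 1.14. I use 1.14 below and check 1.08.

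**Assumed inputs:** exits spread evenly over follow-up; how exit splits between arms; a mean of 15 contacts per patient with SD 10 to 15; lengths of stay.

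**1. Ratio of unadjusted means when the true rate ratio is 1.** If a proportion d leaves evenly over 1.5 years, mean observed time is 1.5 × (1 − d/2).

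| Exit, arm A v arm B | Observed years, A v B | Ratio of mean counts, B/A |
|---|---|---|
| 8% v 8% | 1.440 v 1.440 | 1.00 |
| 6% v 10% | 1.455 v 1.425 | 0.98 |
| 4% v 12% | 1.470 v 1.410 | 0.96 |

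If all exits in the last row happened at the start, the ratio would be 0.88/0.96 = 0.92.

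**2. Effect on a test of mean contacts.** Bias = 15 × (d_B − d_A)/2. SE = SD × √(2 × 1.14/574), which is 0.63, 0.76 and 0.95 for SD 10, 12 and 15.

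- 4% v 12%: bias 15 × 0.08/2 = 0.6 contacts, or 0.95, 0.79 and 0.63 standard errors. Two-sided rejection at nominal 5% is 15.9%, 12.5% and 9.7%.
- 6% v 10%: bias 0.3 contacts. Rejection is 7.6%, 6.8% and 6.2%.
- 8% v 8%: no bias, 5%.

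With a design effect of 1.08 the ranges are 10.0–16.5% and 6.2–7.8%, which is essentially the same.

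**3. Baseline value.** Setting the T3−T0 rule beside Table 1: the admission, service-use and falls rows have no T0 entry, so no subtraction is possible. The expression may be meant as accumulation from T0 to T3, but for quality of life, which is measured at T0, the same expression is a change score.

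**4. Why the denominator for duration matters.** For illustration, treat the 16% and 10% composite figures as the proportions admitted. Suppose the control arm has 6 short and 10 long stays per 100 patients, and the intervention prevents the 6 short ones.

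| Assumed stays | Days per admitted patient, control → intervention | Days per randomised patient, control → intervention |
|---|---|---|
| 2 and 10 days | (12 + 100)/16 = 7.0 → 10.0 | 1.12 → 1.00 |
| 3 and 12 days | (18 + 120)/16 = 8.6 → 12.0 | 1.38 → 1.20 |

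The direction depends on a definition that the protocol does not give.

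**The case against.** Several points on the other side stand.

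- **The rule is not just an unadjusted mean difference.** The section allows means or proportions by type of variable, calls for appropriate tests and adds an adjusted multilevel model. No distribution is named for that model, so it could be adapted to counts, and the exact count family could sit in an analysis plan that is not shown. What remains is that the protocol does fix a contrast and a replacement rule, and an analysis plan that followed both would carry the problem forward.
- **Loss need not truncate the counts.** Service use is to come from records and is assigned in Table 1 to the research team, so a missed visit may not end ascertainment. This lowers the likely size of the problem, but does not help a patient whose records can no longer be followed.
- **The replacement sentence is ambiguous.** It follows the sentence on the 12-month analysis and may apply only there. In that case no replacement rule is stated in this section for the other outcomes.
- **Death is a matter of estimand.** Mean use per randomised patient over 18 months is a legitimate intention-to-treat quantity. A rate over time alive answers a different question, and deaths are reported separately.

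A reader might go further and infer that duration will be compared only among admitted patients, so that preventing short stays would look like harm. The documents do not support this: no denominator is given, and the statement that all analyses follow intention to treat fits total days per randomised patient equally well. Nor do they say that falls will be analysed as a count; a proportion is possible.

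**Conclusion.** The concern holds in a limited form. For non-elective admission episodes and for emergency and primary care contacts, the stated analysis uses no observation time and can let a truncated count stand as an 18-month total. The resulting bias between arms is conditional: none with equal early exit, small at 6% against 10% (6–8% rejection at nominal 5%), and material at 4% against 12% (mean ratio about 0.96; 10–16% rejection). Of these inputs only the 8% overall loss, the numbers of patients and the clustering figures come from the protocol. The split by arm, the timing of exit and the contact distribution are assumed. The missing T0 value and the undefined denominator for duration are gaps in the text whatever the exit pattern. These are secondary outcomes, so the point is worth correcting but does not touch the primary analysis.

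**What to change.** In Analysis of secondary effectiveness:

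- Analyse admission episodes and emergency and primary care contacts as counts over 0–18 months, and again over 0–12 months, instead of as a change from T0. Use a count mixed model, for example negative binomial, with a physician random intercept, the same covariates and log observed time as offset. Report the rate ratio and the rate difference.
- Exclude cumulative counts from the rule that replaces missing values with the latest available data.
- Report deaths by arm beside these results, and state whether observed time stops at death, since that choice defines the estimand.

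In Secondary outcome variables, define duration as total non-elective hospital days per randomised patient over the period, with zero for those not admitted. Treat any mean stay among admitted patients as descriptive.

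The cost is revised wording and slightly more modelling. The offset needs exit dates. The protocol does not expressly say that these are recorded, so this should be confirmed, or the dates added to the case report form.

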#### Calculation of the cost-utility ratio

A cost-utility ratio will be estimated by dividing the total costs by the sum of the potential gains expressed in QALYs. A multivariate sensitivity analysis will be performed by varying the value of the costs with the appropriate distributions within the range of uncertainty. The benefits (QALYs) will also vary with the most suitable distribution in the 95% CIs of the estimates. It will also be included in the sensitivity analysis.

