## Discussion

This pragmatic clinical trial will involve the participation of FPs from over 130 PC health centres in different geographic areas of Spain, thus ensuring a high level of external validity, given that the PC model implemented throughout the country is relatively homogeneous.

Among the possible limitations or biases of our study, we take into consideration that professionals who agree to participate may be more motivated, leading to observer bias (Hawthorne effect). Those professionals more involved in the work will probably make greater use of the DSS than if it were established under normal conditions. If the tool is effective, we might observe an overestimation of the effect that if applied to routine clinical practice would be more limited. This could lead to a greater effectiveness than would be obtained under normal conditions, but it is expected that when randomization is performed after the inclusion of patients in the study, the magnitude of the difference between the two groups will be minimized. Additionally, all physicians will have previously received the training intervention. In this way, it will be ensured that all physicians receive the same training and share the same knowledge of the study, thus reducing performance bias.

The use of a composite endpoint as hospital admission or death is proposed as recommended by some European studies, in order to compare the results with these studies [28, 60, 61].

The intervention cannot be blinded, which could influence the results. However, because the variables can be obtained from records, those who carry out the analysis and their interpretation will not know to which group the patient belongs. In turn, to avoid possible contamination of the professionals in the control group, the intervention group will be advised of their commitment to confidentiality. The control group may use the DSS to review the treatments of the patients included in the study at the end of follow-up for a similar period of time. The expected changes in quality of life are small, but their measurement allows incorporating outcome variables reported by the patient and calculating utilities.

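### The cost-utility result is summarised by a ratio alone although the expected quality-of-life effect is small, and the wording on its uncertainty leaves truncation and joint sampling open

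*Protocol article*

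**What the plan says.** Under Calculation of the cost-utility ratio, the protocol article fixes the summary: "A cost-utility ratio will be estimated by dividing the total costs by the sum of the potential gains expressed in QALYs". For uncertainty it states: "A multivariate sensitivity analysis will be performed by varying the value of the costs with the appropriate distributions within the range of uncertainty". The QALYs are handled in the next sentence: "The benefits (QALYs) will also vary with the most suitable distribution in the 95% CIs of the estimates".

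Three other places bear on this:

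- Analysis of secondary effectiveness gives the QALYs gained "with corresponding 95% CI, as determined using parametric methods and bootstrap techniques".
- Secondary outcome variables sets the QALYs against another cost quantity; they are "compared with the difference between the costs incurred and avoided". The costs incurred are training time, teaching staff, interview time and the rights to use the decision support system. The costs avoided are discontinued drugs and adverse reactions prevented.
- The Discussion says: "The expected changes in quality of life are small".

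**The concern.** A ratio behaves well only when its denominator is clearly away from zero. Here the denominator is a QALY gain that the authors themselves expect to rest on small changes. Once the sampled QALY difference can be negative, the ratio jumps between large positive and large negative values. Its sign also loses meaning: a negative ratio may be a cheaper and better intervention or a dearer and worse one. A wider interval does not cure this; a different summary is needed.

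The wording on uncertainty raises a second question. Both phrases sound like bounds, and costs and QALYs are introduced in separate sentences. If the draws are confined to the 95% CI, or if costs and QALYs are drawn without their correlation, the spread of the result will not be the sampling spread.

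Cost-effectiveness stands beside effectiveness in the abstract's objective and cost-utility is a named secondary aim, so the trial will be read for this result.

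**Working it through.** The documents state no figure for the cost-utility uncertainty, so there is none to reproduce. The sample size serves only to gauge the precision of a QALY difference.

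**Inputs from the protocol article (Sample size)**
- 574 patients per group and 8% loss: 574 × 0.92 = 528 per arm.
- Average cluster of 8 and ICC of 0.02: design effect 1 + (8 − 1) × 0.02 = 1.14. The article prints 1.08, using 5 in the formula; the results below hardly change with that value.

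**Assumed inputs (not in the documents)**
- SD of individual QALYs 0.25 to 0.35.
- True QALY gain 0.01, 0.02 or 0.05.

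**1. How often is the denominator negative?**

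SE = SD × √(2 × 1.14 / 528) = SD × 0.0657, that is 0.0164 at SD 0.25 and 0.0230 at SD 0.35. P(difference < 0) = Φ(−gain / SE).

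| Gain | SD 0.25 | SD 0.35 |
|---|---|---|
| 0.01 | Φ(−0.61) = 0.27 | Φ(−0.43) = 0.33 |
| 0.02 | Φ(−1.22) = 0.11 | Φ(−0.87) = 0.19 |
| 0.05 | Φ(−3.04) = 0.001 | Φ(−2.17) = 0.015 |

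So for gains of 0.01 to 0.02 the range is 11% to 33%. With a design effect of 1.08 it is again 11% to 33%. Cutting the draws at the 95% limits does not help: the range becomes 9% to 32%.

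**2. What this does to the ratio**

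Illustration with assumed incremental cost 200 (SE 100), QALY SD 0.3 (SE 0.0196, from 531.5 per arm) and independent normal draws:

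- gain 0.02: 2.5% and 97.5% limits about −91,000 and +104,000;
- gain 0.05: about −100 and +17,000.

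**3. Effect of bounding the QALY draws**

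- Normal truncated at ±1.96 SE: SD = √(1 − 2 × 1.96 × φ(1.96) / 0.95) = 0.871 SE. The central 95% is ±1.657 SE, and 1.657 / 1.960 = 0.845, so the interval is about 15% too narrow. It covers 2Φ(1.657) − 1 = 0.90.
- Uniform over the CI: SD 1.13 SE, with a central 95% at 0.95 of the proper width.
- Distribution merely scaled by the CI: nothing is lost.

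**4. Effect of independent draws**

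Take cost and QALY uncertainty of equal size in net-benefit units, with correlation ρ. The true variance is proportional to 2 − 2ρ and the independent one to 2, so the SE ratio is 1 / √(1 − ρ):

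- ρ = −0.3: 0.88, that is 12% too small;
- ρ = 0: 1.00;
- ρ = +0.3: 1.20, that is 20% too large.

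With both inputs truncated as well, the ratio is 0.87 at ρ = 0 and 1.04 at ρ = +0.3.

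**The case against.** A reader might infer that the planned uncertainty is simply too narrow. The documents do not support that. The QALY sentence can mean a distribution parametrised by its CI, which loses nothing. The sensitivity analysis is called multivariate, which does not exclude a joint draw. If the draws are independent, a positive correlation makes the result too wide. Nor does the section promise a 95% interval for the ratio, so the 90% coverage figure describes one possible reading.

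A reader might also infer that the QALY bootstrap ignores the family physician. The text is silent on the resampling unit, and silence in an article is not an error. The main model takes the physician as a random factor, and the secondary models follow the same methodology.

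Two further objections stand in part. Several listed costs (training, teaching staff, rights to the tool) belong to the programme or the physician, so a patient-level bootstrap cannot carry all costs, and varying such inputs over distributions is reasonable. And QALYs gained are already to be reported with a CI, so part of a better presentation is in the plan.

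Finally, small is not the same as near zero, and no QALY figure is given. That is correct, and the size of the problem is therefore conditional. An article may leave net-benefit displays and simulation detail to a fuller document, so their absence alone would be no finding. But the ratio is not an omission: it is the cost-utility summary that the article fixes, beside its own expectation of small changes.

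**Conclusion.** The point holds in a limited form. The ratio is a poor sole cost-utility summary for a trial that expects small quality-of-life changes. With an assumed gain of 0.01 to 0.02 QALY and an assumed SD of 0.25 to 0.35, about 11% to 33% of draws have a negative denominator and an interval for the ratio cannot be interpreted. With a gain of 0.05 the share is 1.5% or less.

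The uncertainty may also be misstated, but the direction is open: about 15% too narrow under normal draws truncated at the CI limits, unaffected if the CI only scales the distribution, and wrong in either direction if cost and QALY draws ignore their correlation. The text decides neither question.

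The article also describes the numerator in two ways, as total costs and as costs incurred minus avoided. The change is worth making, but it concerns a secondary objective and leaves the primary analysis and sample size untouched.

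**What to change.** In Calculation of the cost-utility ratio:

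1. Make the incremental cost, the incremental QALYs and the incremental net benefit over a range of willingness-to-pay values the reported summaries. Give the ratio as a point estimate only.
2. Derive their uncertainty by resampling family physicians within arm, carrying each patient's QALYs and patient-level costs (such as drugs) together. Use the full sampling distribution, not draws confined to the 95% CI.
3. Add programme- and physician-level costs (training, teaching staff, rights to the decision support system) per arm, and vary these and the unit prices in the sensitivity analysis.
4. Use one definition of the numerator here and under Secondary outcome variables.

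The cost is a revision of the analysis wording and some programming. No new data are needed. The downside is a possibly wider uncertainty statement.
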